#### 2.6.2. Secondary outcomes.

The secondary outcomes were(i)changes in RVV and.(ii)changes in EVV, both after 8 weeks of meditation, c006Fmpared to control subjects. Any SD1 difference > 1.2 L (Figure S1, Supplemental Digital Content, http://links.lww.com/MD/I272), after 8 weeks of meditation will be considered a clinically significant result.

### 2.7. Data management

Data were downloaded on standardized forms identified by subject number and trial ID. All the data were managed using the RedCap platform. A researcher will conduct an audition of missing or inaccurate data. Data will be backed up daily by automated export procedures from secure servers of the Hospital Maria Aparecida Pedrossian (HUMAP).

### 2.8. Scheme for study retention

Participants will be contacted weekly via phone calls or text messages intended to promote adherence to the study and reschedule missed sessions as much as possible. Attendance will be monitored through session frequency, and adherence will be accounted for as a percentage of fully accomplished interventions.

### 2.9. Safety assessments

All lab tests, evaluations, and interventions in the present study will be performed in a safe environment with a fully equipped emergency resuscitation trolley. Any adverse events that occurred during the study will be monitored to ensure patient safety, and all participants will be monitored. All adverse events will be collected and included in the research reports, which will be forwarded to the Ethics Committee of our institution.

### 2.10. Statistical analysis plan

The 2 groups will initially be compared at baseline in terms of their characteristics, using the chi-squared test for categorical variables and *t*-tests for continuous measures, after Shapiro–Wilk tests for normality. Descriptive analysis will be performed using frequencies and percentages to obtain clinical, anthropometric, and sociodemographic conditions. Two-way ANOVA for repeated measurements will be applied considering between-factors (2 groups) as independent variables and 2 within-factors for BP measurements (gas type and time) as dependent variables (pre-normoxic, pre-hyperoxic, post-normoxic, and post-hyperoxic). A mixed-design with repeated measures will be applied for RCBA, RVV, and EVV as dependent variables in comparing week “0” with week “8.” A post hoc analysis using the Bonferroni procedure, taking into account standard sphericity, will be performed. If this criterion is violated through the Mauchly test, we use the Greenhouse-Geisser correction. In order to explore possible change effects after meditation, coefficients of correlation through Pearson product-moment, including ∆ BP, ∆RVV and ∆ EVV as dependent variables and, ∆RCBA as independent variable, will be performed as percentage of change (∆= (“8 week–“0 week/0 week”)_ *_ 100. Effect sizes (Cohen-d) will also be presented to show the magnitude of our findings, using the scores of 0.20 as small, 0.50 as a medium, and 0.80 as large. Statistical Package for Social Sciences software (version 17.0; IBM Corp, Armonk, NY) was used for all statistical analyses. The study will adopt a *P-value* ≤ 0.05 as statistically significant.

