## 2. Material and Methods

### 2.1. Study design and setting

This was a prospective single-center, parallel-group, randomized, controlled trial with concealed allocation and with 8 weeks of follow-up analyzed using an intention-to-treat approach. The study will be performed at the Laboratory of Respiratory Pathophysiology (LAFIR) at the Respiratory Division of the University Hospital (HUMAP) and the comprehensive care and monitoring of persons with hypertension in primary health care. This will be performed according to the SPIRIT (2013) guideline checklist and recommendations. A Schedule of enrollment, interventions, and assessments from the SPIRIT guidelines is shown in Figure 1.

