#### 2.4.3. Exclusion criteria.

Subjects will be excluded according to the following criteria:(1)subjects who did not adhere to the experimental protocol.(2)had an important comorbidity, such as heart failure ≥ NYHA I, COPD, cognitive impairment (mini-mental exam < 27 points) or psychiatric disease, previous stroke, neuromuscular disease, asthma, uncontrolled diabetes, peripheral vascular disease, obesity grade III, renal failure of stage > 2 with glomerular filtration rate < 60 mL/minutes/1.73 m2, sleep apnea, malnutrition (BMI < 18.4) or other diseases that interfere with the performance of the protocol.(3)missing more than 2 weekly based supervised meditation sessions.(4)secondary hypertension.(5)contraindications to perform a symptom-limited maximal exercise test; and.(6)regular meditation practice.

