#### 2.4.6. Sample size.

Since there are no previous studies on CB activity after meditation, our a priori sample size calculation was based on a previously cited pilot study on RCBA ^[47]^. Considering an effect size of 0.25, a minimum of 30 subjects would be necessary to detect a significant change in chemoreception based on within-group analysis. In addition, the sample size was calculated based on a pilot study. The pilot study comprised 12 normotensive/prehypertensive healthy subjects and showed a standard deviation of the mean difference for SBP ± 4.2 mm Hg, during 2 different trial days (see Supplemental Digital Content, http://links.lww.com/MD/I272), with the oscillometric method and under the same experimental conditions (normoxic, see subsection 2.5.7). Based on a repeated measure ANOVA design with 1 between-group factor (Meditators vs Control) and 2 within-groups factors (Gas type and Time), with 4 averaged BP measures [pre-normoxic (T1), pre-hyperoxic (T2), post-normoxic (T3), post-hyperoxic (T4)] for each subject, upon resting condition, 30 subjects per group would be adequate in a 2-sided study to set an error type I = 0.05 and *β* = 0.80. Considering a 20% dropout and exclusion rate, a minimum total sample size of 36 per group was required. This sample size is concordant with several studies on the effects of meditation on hypertension.^[47]^

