### 2.6. Outcomes

For participants who dropped out of the study at any time after randomization, researchers will use contact details to encourage them to undergo the end-study outcome assessments (8-weeks). Thus, outcomes will be assessed before and after the intervention period, regardless of attending or completion status.

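### The repeated-measures ANOVA leaves out baseline adjustment and by default uses complete cases only; a constrained-baseline mixed model would be more precise and fit the intention-to-treat aim better

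*Protocol article*

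**What the plan says.** Section 2.10 fixes the model for BP: "Two-way ANOVA for repeated measurements will be applied considering between-factors (2 groups) as independent variables and 2 within-factors for BP measurements". The dependent variables are the four cells "pre-normoxic, pre-hyperoxic, post-normoxic, and post-hyperoxic". On sphericity it adds: "If this criterion is violated through the Mauchly test, we use the Greenhouse-Geisser correction". Together these describe a classical repeated-measures ANOVA in which baseline is part of the response.

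For resting carotid-body activity (RCBA), which is the third primary outcome, and for resting and exercise ventilatory variability (RVV, EVV), the same section says: "A mixed-design with repeated measures will be applied for RCBA, RVV, and EVV as dependent variables", comparing week 0 with week 8. No baseline covariate is named for any outcome.

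Two other statements bear on this. Section 2.1 says the trial is "analyzed using an intention-to-treat approach". Section 2.6 commits to following up dropouts, so that "outcomes will be assessed before and after the intervention period, regardless of attending or completion status".

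**The concern.** Three features of the named method deserve attention.

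- **Precision.** With one value before and one after, the group x time term in a repeated-measures ANOVA is the two-sample comparison of change. Adjusting for baseline never has a larger asymptotic variance, and has a smaller one unless the correlation is perfect. The baseline values are being collected anyway.
- **Incomplete participants.** Classical repeated-measures ANOVA needs all four BP cells. Unless something else is specified, a participant without week 8 contributes nothing, not even a baseline. The plan aims to analyse everyone randomised, so this is an awkward default.
- **The contrast of interest.** Primary outcomes (i) and (ii) in section 2.6.1 are group differences in BP change within each gas, and section 1.2 poses an interaction between gas and meditation. Section 2.10 does not say which ANOVA term or contrast answers each question.

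At stake is some power in a trial planned on 30 analysable participants per arm, and a clear estimate for each primary BP outcome.

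**Working it through.** **Inputs from the article.** Section 2.4.6 gives 30 per group needed, 36 per group to be enrolled, two-sided alpha 0.05, and an SD of the within-person SBP difference of 4.2 mm Hg. That SD comes from 12 normotensive or prehypertensive people measured on two days under normoxia. The stated beta of 0.80 is read as power 0.80. No target BP difference and no correlation are given.

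**The plan's own figure.** Without a target difference, 30 per group cannot be reproduced. It can be inverted, using the change-score SD of 4.2:

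detectable difference = 4.2 x sqrt(2/30) x (1.96 + 0.84) = 3.04 mm Hg.

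So 30 per group is consistent with a change-score comparison aimed at about 3 mm Hg. The 36 is 30 x 1.2.

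**Gain from adjustment.** Let the SD be s at both times and the correlation rho. Per participant:

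- change score: variance 2s²(1 - rho)
- baseline-adjusted: variance s²(1 - rho²)
- ratio: (1 - rho²) / [2(1 - rho)] = (1 + rho)/2

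Rho has to be assumed. One route is to take it directly. The other is to take the pilot SD of difference at face value and assume a between-person SBP SD s: 4.2² = 2s²(1 - rho), so rho = 1 - 17.64/(2s²). For s = 6 this is 1 - 17.64/72 = 0.755.

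Equivalent n is 30/ratio. Power is the normal probability below 2.80/sqrt(ratio) - 1.96, where the change-score test has 0.80.

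| Assumption | rho | Variance ratio | 30 per arm acts like | Power |
|---|---|---|---|---|
| rho set directly | 0.50 | 0.75 | 40 | 0.90 |
| rho set directly | 0.70 | 0.85 | 35 | 0.86 |
| s = 6 mm Hg | 0.76 | 0.88 | 34 | 0.85 |
| s = 8 mm Hg | 0.86 | 0.93 | 32 | 0.83 |
| s = 10 mm Hg | 0.91 | 0.96 | 31 | 0.82 |
| s = 12 mm Hg | 0.94 | 0.97 | 31 | 0.81 |

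Simulation at rho 0.5, 0.7 and 0.8, with a true difference of 3.09 mm Hg and 30 per arm, agreed. Power was 0.81, 0.81 and 0.80 for group x time, and 0.89, 0.85 and 0.83 with baseline adjustment.

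**Complete-case analysis and bias.** A second simulation took a true effect of -3.0 mm Hg with about 20% of week-8 values missing.

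| Missingness (assumed) | Complete-case change score | Baseline-adjusted |
|---|---|---|
| Completely at random | -3.0 | -3.0 |
| Depends on baseline, same way in both arms | -3.0 | -3.0 |
| Depends on baseline, opposite ways by arm | -2.25 to -2.53 | -3.0 |

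Bias in the change score appeared only in the last case, which is an assumption and not something the article indicates.

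**Labels and sphericity.** Group, gas and time are three factors, although the text says two-way. Read as 2 x 2 x 2, every within-person effect has one degree of freedom. Sphericity then holds automatically and the Mauchly and Greenhouse-Geisser step changes nothing. The same is true of week 0 against week 8 for RCBA, RVV and EVV. Read instead as group by one four-level condition, sphericity does matter, but the resulting 3-df interaction is not one of the stated primary comparisons.

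**The case against.** The defence is substantial, and several stronger readings do not survive it.

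- **That intention to treat is contradicted outright.** A reader might infer this, but the article nowhere says incomplete participants are dropped. Deletion is a default of the method. Handling of missing data may sit in a fuller plan that is not shown, and section 2.6 actively seeks week-8 values from dropouts. What stands is a poor fit, not a contradiction. The exclusion in section 2.4.3 for "missing more than 2 weekly based supervised meditation sessions" is a more direct tension with intention to treat, but it is a separate matter that no choice of model would cure.
- **That about 7 of 36 per arm would be discarded by the ANOVA.** Section 2.4.6 says: "Considering a 20% dropout and exclusion rate, a minimum total sample size of 36 per group was required". That rate mixes dropout with exclusion. Dropouts may still supply week-8 data, and excluded participants are lost through the eligibility rules whatever the model. Loss of a single gas condition is also speculative, since both are run in sequence at one visit.
- **That the test is invalid, or that having baseline as a response is itself the fault.** Group x time is a legitimate randomised comparison which uses baseline by subtraction. A constrained-baseline model also keeps baseline as a response and loses nothing. The loss comes from leaving the baseline means unconstrained and unadjusted.
- **That the gain is 15 to 25% of variance.** This needs rho of 0.5 to 0.7. The article's only repeatability figure points higher, to a gain of about 3 to 12%. That figure comes from a small, non-hypertensive, short-interval pilot, so rho over 8 weeks could be lower.

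It is also fair that the study calls itself exploratory, that Bonferroni post hoc comparisons offer a route to within-gas contrasts, and that the three-way interaction does address the hypothesis in section 1.2. The exact contrast for each primary outcome is still not named.

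**Conclusion.** The concern holds as a question of efficiency and fit. The planned ANOVA gives a valid but unadjusted change-score comparison. It gives up between about 3% and 25% of variance, so that 30 per arm with adjustment acts like about 31 to 40. The lower end follows from the pilot SD of 4.2 mm Hg with an assumed between-person SD of 12 mm Hg, and the upper end from an assumed rho of 0.5. Equal variances at the two times are assumed throughout. The complete-case default suits neither the intention-to-treat statement nor the effort to follow up dropouts, but the article does not show how many participants this would affect, or that it would cause bias. The factor label and the sphericity step are tidying points that alter no result under the 2 x 2 x 2 reading.

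**What to change.** In section 2.10, replace the BP ANOVA with a likelihood-based linear mixed model on all available values, fitted separately to SBP and DBP.

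- **Mean terms:** time, gas, gas x time, arm x time and arm x gas x time. Include no arm or arm x gas term at baseline, so that baseline means under each gas are constrained equal across arms.
- **Covariance:** allow correlation among each participant's four values.
- **Report:** the meditation-control difference at week 8 with 95% CI under normoxia (primary outcome i), under hyperoxia (primary outcome ii), and the difference between these two (the interaction hypothesis of section 1.2).
- **RCBA, RVV and EVV:** use the same constrained-baseline model, or ANCOVA on the week-8 value with baseline as covariate.
- **Delete** the Mauchly and Greenhouse-Geisser step.

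For BP, the constrained model is preferable to a week-8 model with baseline as covariate, because the latter still omits anyone without a week-8 value. The constraint presumes that baseline is measured before allocation is revealed. Section 2.4.4 says so, but section 2.2 places the visits after randomization, so the text should confirm it.

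The cost is analysis wording only. No extra data, visits or participants are needed, and mixed models are available in the named software.

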### 1.2. Study aims and outcomes

Thus, suspected hyperactivity of CB beyond hypoxic states would be a straightforward pathway to investigate mechanisms underpinning anti-stress therapies in HT, which could theoretically decrease the hierarchical-dependent influence of CB. This exploratory study aimed to investigate the putative role of CB in the decrease in BP and changes in ventilatory variability that could occur in response to meditation. Hence, the primary outcome of this study was to detect changes in BP and CB activity after 8 weeks of meditation. The secondary outcomes were changes in rest and exercise ventilatory variability. We anticipate that interactions between hyperoxic deactivation of CB and meditation at 8 weeks; Will reduce BP beyond stand-alone intervention, or alternatively; Meditation will significantly attenuate the effects of hyperoxia as a stand-alone intervention for BP. In addition, breathing variability could change, partially mediated by a reduction in CB activity.

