#### 2.5.9. RCBA.

Resting CB activity will be measured through a hyperoxic trial (FIO_2_ = 100%) after ensuring stable minute ventilation (5-minutes of normoxic calm breathing). Baseline minute ventilation is the average value of the last 60 seconds of breath-by-breath stable ventilatory signal. During the next 1-minute hyperoxic trial delivered through a non-rebreathing system, the nadir of 10 seconds averaged minute ventilation was measured.^[54]^ The test was repeated 3 times (3-minutes apart), and the average value was considered (Protocol 3, Fig. 3). The lowest value is taken as an index of basal CB activity, and a greater reduction in minute ventilation corresponds to a greater tonic input from the carotid body.^[54]^

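### The exploratory carotid-body correlations use percentage changes with no arm term: if RCBA is a fall in ventilation this can hide a true link, and if the arms are pooled it can create a false one

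*Protocol article*

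**What the plan says.** Section 2.10 introduces the analysis with "In order to explore possible change effects after meditation" and specifies "coefficients of correlation through Pearson product-moment". The dependent variables are the changes in BP, RVV and EVV. The correlations, with the change in "RCBA as independent variable, will be performed as percentage of change", defined as (week 8 − week 0)/week 0 × 100. The section gives no arm term, stratification or partial correlation, and does not say whether the correlation uses both arms or the meditation arm only.

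Section 2.5.9 describes RCBA in two ways. It defines a normoxic reference ("Baseline minute ventilation is the average value of the last 60 seconds") and says that "a greater reduction in minute ventilation corresponds to a greater tonic input from the carotid body". That makes RCBA a difference between two ventilations. It also says "The lowest value is taken as an index of basal CB activity", which read literally is the nadir ventilation itself.

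Section 1.2 calls the study exploratory and anticipates that "breathing variability could change, partially mediated by a reduction in CB activity".

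**The concern.** There are two separate mechanisms, and they act in opposite directions.

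- **Unstable denominator.** If RCBA is a fall, the week-0 value can be small. Dividing by it gives a few participants very large percentages, and Pearson's r is sensitive to such points. The main effect is to hide a true link.
- **Pooling without arm.** If meditation lowers both BP and RCBA, pooling the arms yields a correlation even when, within each arm, the people whose RCBA changes most are not those whose BP changes most.

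This correlation is the only planned analysis that relates RCBA change to change in BP, RVV or EVV. An unreliable result would therefore weaken what the trial can say about the carotid body's part in any effect.

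**Working it through.** The document attaches no figure to this analysis, so there is none to reproduce. The check asks how the stated method behaves against arm-adjusted absolute change.

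**Inputs from the document.** 30 analysable per group, SD of SBP difference 4.2 mm Hg, two-sided 0.05 (2.4.6); BP change called clinically significant, 5.9 mm Hg (2.6.1).

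**Assumed, because the document gives no RCBA mean or SD.** True baseline fall with mean 1 to 4 L/min and between-person SD 1; measurement error SD 0.5 per visit; SD of true change 0.5; meditation effect on RCBA 0.8 L/min; baseline SBP 145 (SD 8); for the nadir reading, resting ventilation 10 (SD 1.5) L/min and a mean fall of 2.

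**1. Denominator.** The same 0.5 L/min reduction is −17% from a fall of 3 (0.5/3) and −50% from a fall of 1 (0.5/1). The observed baseline has SD √(1² + 0.5²) = 1.118. P(baseline ≤ 0) = Φ(−mean/1.118), which is 0.4%, 3.7% and about 18.5% for means of 3, 2 and 1. For those people the percentage is undefined or has its sign reversed.

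**2. Pooling, by hand on absolute change.** The observed RCBA change has SD √(0.5² + 0.5² + 0.5²) = 0.866. The arm shifts in SD units are 0.8/0.866 = 0.924 (RCBA) and 5.9/4.2 = 1.405 (SBP). With 1:1 arms and no within-arm correlation,

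r = (δx·δy/4) / √[(1 + δx²/4)(1 + δy²/4)] = 0.3245 / √(1.213 × 1.493) = 0.24.

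The critical |r| for 60 people is 0.254, so nearly half of trials would be significant. Simulation gives 47-48%.

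**3. Simulation, 10,000 trials per setting.** False links: no within-arm link, with meditation effects of 0.8 L/min and 5.9 mm Hg. Power: true latent correlation 0.6, no arm effects.

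| Mean fall (L/min) | False link, pooled % change | Power, % change | Power, absolute change |
|---|---|---|---|
| 3 | 32% | 51% | 78% |
| 2 | 13% | 21% | 78% |
| 1.5 | 8% | 12% | 79% |
| 1 | 6% | 8% | 79% |

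At a mean fall of 4, power on the percentage scale is 69%. Centring within arm brings the false-link rate to 4.7-5.4% in every no-link setting. As the denominator worsens, the pooled false link shrinks while the loss of power grows.

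**4. Other assumed values.** The error model in step 3 is crude. A further set of runs over mean falls of 1 to 3 L/min gave power of 88-98% on absolute change against 12-98% on percentage change. Pooled false links were 7-68% on percentage change, against about 5% with arm adjustment. Absolute change detected the true link more often in every setting.

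**5. Nadir reading.** If RCBA is the lowest ventilation, the divisor is far from zero and little power is lost (74% on percentage change, 79% on absolute). Pooling still gives a false link in 43% of trials on the percentage scale.

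**The case against.** The strongest reply is that the problem rests on two readings that the text does not settle. Section 2.5.9 can be taken to make the nadir the index, and the opening phrase in section 2.10 can mean the meditation arm alone. Under both of those readings together the problem largely disappears. That stands, and neither the fall nor the pooling should be treated as stated fact. Three of the four combinations still leave a problem, and the protocol does not choose the harmless one.

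Three stronger claims are tempting and are not supported:

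- **That this is the only test of the trial's central question.** The group × gas × time ANOVA for BP also probes carotid-body involvement, by deactivating it with hyperoxia in both arms, and RCBA is itself compared between arms. The correlation sits beside these.
- **That the errors are extreme.** With an assumed mean fall of 1.5 L/min and symmetric error, one can get 1-5% non-positive baselines and largest changes of 350-900% among 60 people. But section 2.5.9 takes the lowest 10-second average, which pushes the fall above zero, and averages three trials. Modelled that way, the figures are about 0.2% and 130-170%. Likewise, arm shifts of 0.8-1.0 SD give false links in 18-34% of trials, but for absolute change. The same inputs on the planned percentage scale give 8-17%.
- **That the plan claims to prove mediation by correlation.** Section 1.2 states mediation as an expectation. Section 2.10 never says that the correlation tests it.

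A condensed article may leave arm handling to a fuller plan. It does, however, commit to a percentage scale and a simple Pearson coefficient, and those are stated choices.

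**Conclusion.** The point holds in conditional form. The percentage scale and the unadjusted Pearson coefficient are stated. The harm from the scale depends on RCBA being a fall, which is the more natural reading because a reference ventilation is defined and its reduction is interpreted. The harm from the missing arm term depends on pooling, which is left open.

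The size cannot be fixed from the document. The headline ranges in step 4 run from almost no loss of power to loss of most of it, and from a near-nominal false-link rate to one above half. The cruder model in step 3 gives lower power on both scales and the same ordering. These figures show a range under assumed RCBA values and do not predict this trial. Section 2.6.1 itself notes that no RCBA reproducibility study in hypertensive adults is known, so there is no basis for assuming the favourable end.

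This is worth correcting, but it concerns an exploratory analysis. The primary between-group comparisons of BP and RCBA do not depend on it.

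**What to change.** In section 2.5.9, state whether RCBA is the fall from reference ventilation or the nadir. In section 2.10, replace the percentage-change correlations with a regression of absolute change (or the week-8 value adjusted for baseline) in BP, RVV and EVV on absolute change in RCBA, with arm and the baselines as covariates. Report the slope with its 95% CI and describe it as an association, not as mediation.

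Make both changes together. In the runs above, moving to absolute change while pooling without arm raised the false-link rate, for example from 32% to 47% at a mean fall of 3 L/min.

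The cost is a sentence or two. No new data are needed and the primary analyses stay as they are.
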